### Data management and security

There will be three modes of data collection in this research study: in-person, pedometer and mobile phone. All questionnaire data instruments will be collected on machine-readable data forms based on the Cardiff Teleform software system. Completed teleforms will be faxed to the San Francisco Coordinating Center where a server using optical character recognition (OCR) technology will verify and store the data in the study database on a secure Microsoft SQL server. A standardized procedure will convert the SQL data to SAS data.

Data from participant's pedometers will be downloaded at the research office and electronically transferred to the San Francisco Coordinating Center. Data from the mobile phone is collected in real-time on the mobile phone's memory card, time-stamped and stored for transmission over a wireless network to a secure server. A secure online data management service, SugarCRM^®^, will be used to capture the mobile phone data. Each night, after using the physical activity diary, the participant will be prompted to exit the application, at this time the data will be transmitted to SugarCRM^®^. These data will all be encrypted. If the wireless network is unavailable, data will be stored on the mobile phone and transmitted when the wireless network next becomes available. A daily report is generated by SugarCRM^® ^and reviewed daily by the research team to monitor compliance with the mobile phone trial application. Both the mobile phone and data storage will Health Insurance Portability and Accountability Act (HIPPA) compliant. All participants will be assigned a study identification number immediately after enrollment; this identifier will be used on all study data.

### Statistical analysis and power calculation

The primary analyses will be by intention-to-treat, without regard to adherence to intervention protocols. We will use linear mixed models to compare trends in the primary and secondary endpoints. To avoid inflating the type-I error rate, differences in the maintenance period will be tested only if the intervention is shown to be successful during the trial. If dropout is substantial, sensitivity analyses will be conducted in which we multiply impute missing outcome data under the conservative assumption that exercise levels fall back to their baseline levels after study dropout. The validity of the randomization will be assessed by comparing randomized groups on characteristics measured before each randomization. If potentially confounding imbalances are found, we will adjust the between-group analyses for potential confounders of treatment assignment.

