### Study aims

The aims of this RCT are threefold: 1) to assess the efficacy of the 3-month mobile phone and pedometer based physical activity intervention on increasing physical activity compared to the control group; 2) to compare the efficacy of the 6-month maintenance intervention-PLUS to the 6-month maintenance intervention-REGULAR; and 3) to explore the role of potential mediating factors (self-efficacy for physical activity, social support, and barriers for physical activity) and moderating factors (body mass index and age) on changes in outcomes at 3, 5, 7 and 9 months. The primary outcome measure for the first two aims is the total steps per day as measured by the Omron Active Style Pro HJA-350IT (triaxial accelerometer) pedometer.

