### Screening/Baseline visit and run-in period

All potential subjects will be screened by telephone and eligible subjects will be invited to attend a screening/baseline visit. After obtaining a written informed consent, baseline data will be gathered to determine eligibility. Eligible participants will be issued a mobile phone and pedometer; training will be provided to insure participants can successfully use both devices. During the 3-week run-in, the pedometer will be set to record and store physical activity (e.g. steps), but no display of steps will be visible (only date and time will be visible) on the pedometer. A run-in mobile phone application has been created specifically for this phase of the study; it is designed to mimic the intervention application without any content to encourage or support increasing physical activity.

The run-in period has two purposes: 1) to determine the baseline average daily steps and 2) to determine if the participant will be able to comply with the requirements of the study. In order to be eligible for randomization, participants must successfully complete a fasting blood test at a research lab in addition to completing the run-in period with at least an 80% adherence rate in each of the following: 1) daily message responses, 2) daily activity diary responses, and 3) pedometer wearing time of at least 8 hours per day.

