### Randomization

One hundred and ninety-two women will be randomly assigned in a 1:1:1 ratio to the PLUS, REGULAR or CONTROL groups. Permuted-blocked randomization will be used to ensure that the number of participants in the three treatment groups is close to our goal of an exact 1:1:1 ratio. Block size will vary randomly from three to nine in a schedule that is not known to investigators and research staff. The data management staff will prepare a set of sealed, opaque envelopes, numbered consecutively, and containing the study group assignment.

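### Covariate adjustment is made to depend on baseline imbalances found after randomisation, with no covariates, measure or threshold fixed in advance

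*Protocol article*

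**What the plan says.** The section on statistical analysis and power calculation takes three steps.

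- Primary model: "We will use linear mixed models to compare trends in the primary and secondary endpoints". The fixed terms of that model are not listed.
- Baseline check: "The validity of the randomization will be assessed by comparing randomized groups on characteristics measured before each randomization".
- Consequence: "If potentially confounding imbalances are found, we will adjust the between-group analyses for potential confounders of treatment assignment".

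Other sections bear on this. Under Randomization, "One hundred and ninety-two women will be randomly assigned in a 1:1:1 ratio to the PLUS, REGULAR or CONTROL groups", using permuted blocks of randomly varying size and sealed, opaque, numbered envelopes; no stratification factor is mentioned. The run-in exists partly "to determine the baseline average daily steps", so every randomised woman has a pre-randomisation value of the primary outcome. Age and BMI are also known for everyone, and the study aims name them as possible moderators. The Blinding section says that participants, research staff and investigators cannot be blinded.

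**The concern.** This is a rule that the article states, and not a detail left to a later analysis plan. A plan that follows it inherits the problem, and one that names fixed covariates contradicts it.

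The rule has three weaknesses. First, if allocation is carried out as described, any baseline difference between arms is chance, so finding one says nothing about whether randomisation was valid. Second, a covariate earns its place in the model by how well it predicts daily steps. A predictive covariate that happens to look balanced is omitted under this rule, although adjusting for it would still sharpen the comparison. Third, with no list, measure or threshold, someone must decide after randomisation what counts as an imbalance and as a potential confounder, and the staff and investigators know the assignments.

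At stake are the prespecification of the between-group analyses and some precision.

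**Working it through.** **The plan's own figures.** The sample size section gives 114 women for 90% power at 1100 steps, but no SD, within-subject correlation or alpha, so 114 cannot be reproduced forwards. Assume two-sided alpha of 0.05, so that 1.960 + 1.2816 = 3.2415. The implied SD is (1100/3.2415) × √(n/2) per arm:

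- no dropout, n = 57: SD about 1812
- 75% retained, n = 42.75: SD about 1569

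For the 3-month comparison at 88% retention, the evaluable numbers are 128 × 0.88 = 112.6 and 64 × 0.88 = 56.3. The standard error is SD × √(1/112.6 + 1/56.3) = SD × 0.163. Power for 1000 steps is then 92.3% (SD 1812) to 97.4% (SD 1569), and above 99.9% for 2200 steps. The stated powers agree with one another and do not rely on covariate adjustment.

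**How often a screen would find something.** The Study measures section lists about 24 baseline characteristics: 8 sociodemographic, 4 on history, smoking, alcohol and medication, 6 from the physical examination, and 6 blood tests. It also names five questionnaires. With k independent variables and an assumed p<0.05 threshold, the chance of at least one flag is 1 − 0.95^k: 23% for k = 5, 40% for k = 10 and 64% for k = 20. Many of these variables are correlated (weight with BMI and waist, for example), so this only illustrates that some flag is likely.

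**What the rule does to error and power.** Take one covariate with correlation r to the outcome, given what the model already contains. Let z be its standardised imbalance, distributed N(0,1). In large samples:

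- unadjusted statistic given z: N(d + r·z, 1 − r²)
- adjusted statistic: N(d/√(1 − r²), 1)
- rule: use the adjusted statistic only if |z| > 1.96

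Set d = 0 for type I error and d = 3.2415 for 90% unadjusted power. Example at r = 0.5: 3.2415/√0.75 = 3.743, and 3.743 − 1.960 = 1.783, which is 96.3% power if adjustment is always made. Averaging over z for the rule gives:

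| r (assumed) | Type I error, rule | Power, rule | Power, always adjusted |
|---|---|---|---|
| 0.2 | 4.9% | 90.2% | 91.1% |
| 0.3 | 4.8% | 90.4% | 92.5% |
| 0.5 | 4.3% | 90.9% | 96.3% |
| 0.6 | 4.0% | 91.3% | 98.2% |

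A finite-sample simulation (113 against 56 women, 20,000 runs, effect of 0.5 SD) shows the same pattern. At correlation 0.5 the rule has type I error 4.1% and power 87.0%, against 93.7% for always adjusting.

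**Conditional on the imbalance.** Unadjusted type I error given z is P(|N(r·z, 1 − r²)| > 1.96). At z = 1.5, which would not trigger adjustment, it is 8.2% (r = 0.5) or 9.3% (r = 0.6). At z = 0 it is 2.4% or 1.4%. These deviations offset one another, and the average lies a little below 5%.

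**The case against.** The strongest reply concerns precision. The primary model is a linear mixed model of trends, and the sample size used a within-subject correlation, so run-in steps may already be in the model as the time-zero response. The article does not list the terms, and a condensed article need not. This stands. A reader might infer that the precision available from run-in steps is mostly lost, but the documents do not show that. If run-in steps are already used, r describes what age or BMI adds, and the top rows of the table apply: a gain of one or two points. The article names age and BMI as possible moderators, not as established predictors.

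The 90% starting point is also low for this trial. With 64 per arm, PLUS plus REGULAR has 128 women and not 114, which gives about 93% power (3.2415 × √(128/114) − 1.960 = 1.475). The 3-month comparison has almost nothing to gain at 2200 steps.

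A reader might also infer that the rule inflates type I error. Applied mechanically it does not. Error would rise, to between 6.2% and 8.3% in the simulation for correlations of 0.3 to 0.7, only if the more favourable of the adjusted and unadjusted results were picked. Nothing in the article says that this is intended; the undefined trigger merely leaves room for it.

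Finally, the text says potentially confounding imbalances, which implies some regard to the outcome, and it mentions no p-value. Both are fair points, and the p<0.05 trigger used here is an assumption. But no criterion replaces it, and a predictive covariate that looks balanced is still left out.

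**Conclusion.** The concern holds as a fault in a stated analysis rule. Adjustment depends on imbalances found after randomisation, by criteria that are not given, in a trial whose staff and investigators know the assignments; and the baseline comparison cannot bear the meaning given to it as a test of randomisation.

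The numerical cost is modest and uncertain: about 1 to 7 percentage points of power for r from 0.2 to 0.6, starting from 90%, and near the low end if run-in steps are already in the mixed model. These figures rest on an assumed r, an assumed p<0.05 trigger, a single covariate and two-sided alpha of 0.05. They do not show that the stated powers are wrong.

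The change is worth making because it removes a post-hoc choice at almost no cost.

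**What to change.** - Delete the imbalance-triggered adjustment and the sentence that treats baseline comparison as a check on the validity of randomisation.
- State in advance how run-in mean daily steps enter the mixed model, either as a covariate or as the time-zero response, and that age and BMI are always included whatever the observed balance. Make this the primary model.
- Present baseline characteristics by arm descriptively only.
- Adjustment of PLUS against REGULAR for steps just before the 3-month visit could be a prespecified sensitivity analysis. It should not be in the primary model without further argument: it is measured after randomisation, and only 88% are expected in follow-up at 3 months.
- Reconcile the wording of the baseline check, which implies more than one randomisation, with the Randomization and Physical activity maintenance sections, which describe a single assignment at the randomisation visit. If the phrase meant the start of maintenance, the characteristics compared would be post-randomisation.

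The cost is one or two sentences of analysis wording. Run-in steps, age and BMI are already collected, and neither sample size nor conduct changes.

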#### Sample size and power

We assumed that the net effect of the intervention would be to increase average daily steps by 2200, based on our pilot data and recently published review papers [22,23]. During the maintenance period, we assumed that the difference between PLUS and REGULAR maintenance groups would be 1100 steps. We used data from the Woman's Exercise Injuries: Incidence and Risk Factors (WIN study) [24] to estimate the standard deviation and within subject correlation of the primary outcome. Finally, we assumed that 88% of participants would remain in follow-up at 3 months and that 75% would remain in follow-up at 9 months. To provide 90% power to detect a between-group difference of 1100 steps per day in the maintenance period, we will require that 114 women be randomized in a 1-1 ratio to the PLUS and regular maintenance groups. The overall sample size of 192 for the trial will provide more than 95% power to detect a between-group difference of 2200 steps, and more than 90% power for net differences as small as 1000 steps.

## Discussion

The purposes of this randomized controlled trial are to test the efficacy of a 3-month mobile phone and pedometer based physical activity intervention and to compare two different 6-month maintenance interventions. In this RCT, the mobile phone serves multiple purposes: the means of delivering the physical activity intervention: sets individualized weekly physical activity goals: provides self-monitoring (diary); provides immediate feedback, social support, and real-time data capture. To our knowledge, this is the first mobile phone based physical activity intervention to incorporate all functions listed above. It is also the first to use a RTC design to test the efficacy of such an intervention in a diverse sample of physically inactive women. This RCT design has several unique features and may add new knowledge to current behavioral sciences. One of the strengths of this RCT is the length of mobile phone use. Specifically, a 3-month mobile phone and pedometer based intervention, followed by a 6-month active maintenance intervention (PLUS or REGULAR) exceeds the length of most previous trials [7-10,25-32]. In addition, by utilizing two different physical activity maintenance interventions, this study has the potential to make a major contribution to our understanding of maintenance strategies in terms of a dose-response with or without a mobile phone diary component. Lastly, the combination of objectively measured downloadable physical activity (e.g. steps, duration, and intensity) data and the time-stamped mobile phone data will allow the research team to better understand the efficacy and mechanism of the physical activity mobile phone intervention among physically inactive women.

A few limitations of this study need to be acknowledged. First, although J2ME and iPhone applications are available in this RCT, the physical activity intervention is incompatible for all mobile phone platforms. If a participant has an incompatible mobile phone, she will be required to use a study mobile phone for the duration of the study intervention in addition to her own mobile phone. This may potentially reduce adherence to the mobile phone based intervention over a longer period of time, although our pilot study showed excellent adherence over a three week period. A second limitation of this study is that Omron Active Style Pro HJA-350IT (triaxial accelerometer) pedometer is unable to capture and record physical activity data from bicycling, swimming or yoga. Therefore, we will also use the Seven-Day Physical Activity Recall questionnaire to capture these activities at 3, 7, 9 and 12 months. In addition, the mobile phone diary will include a question as to how long subjects engage in these activities, if applicable.

## Abbreviations

AE: Adverse event; BMI: Body mass index; CES-D: Center for epidemiological studies depression scale; DSMB: Data safety and monitoring board; HDL: High density lipoprotein; HIPPA: Health insurance portability and accountability act; iOS: i operating system; IRB: Institutional review board; J2ME: Java 2, micro edition; Kg: kilogram; LDL: Low density lipoprotein; MET: Metabolic equivalent of task; mHealth: Mobile health; mPED: Mobile phone based physical activity education; OCR: Optical character recognition; PAR: Seven-day physical activity recall; RCT: randomized controlled trial; RGL: Reading grade level; SAS: Statistical analysis system; SF-12: 12-item Short-form health survey; SPSS: Statistical package for social science; UCSF: University of California, San Francisco; WIN: Woman's Exercise Injuries: Incidence and Risk Factors.
